### Secondary outcome measures

2.8

1.Quantitative measurement of children intelligence-related scalesThe intelligence development scale of Bayley scales of infant development^[22]^ is used to evaluate the intelligence of children with cerebral palsy. It will be independently completed by the special efficacy evaluation team of each hospital.2.The overall health of children with cerebral palsy

The 4 diagnostic scales of Chinese medicine will be used to record the symptoms of the children, such as diet, sleep, and diarrhea. Regarding the Chinese medicine new medicine clinical research guiding principles^[23]^ and journal of pediatrics of traditional Chinese medicine^[24]^ to develop the 4 clinical observation integral scale of Traditional Chinese Medicine type spasm cerebral palsy, from 4 aspects: inspection, auscultation and olfaction, inquiry, and pulse-taking and palpation of children with the breath, color, shape, state, god, crying, eating, sleeping, mainland, and so on, a comprehensive evaluation of various combined score values (single 2 points, a total of 27 items, maximum 54 points) will be performed.

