### Subject recruitment

2.3

Inclusion criteria:

(1)Aged 1 to 3 years, both male and female children.(2)Grading of the large motor function at the I-III level.^[15,16]^(3)Children who meet the diagnostic criteria for spastic cerebral palsy.^[17]^(4)Muscle tone between I-IV (according to the newly revised Ashworth scale).(5)Follow the doctor advice during the study and insist on receiving the tester.

Exclusion criteria:

(1)Those with severe mental illness and severe epilepsy.(2)Organized diseases involving other organs such as the heart, liver, and kidney.(3)Exclusion of leukodystrophy, infantile spinal muscular atrophy, spin cerebellar ataxia, genetic metabolic diseases such as phenylketonuria, congenital cretinism, and congenital hydrocephalus.(4)Failure to meet the inclusion criteria, failure to complete the test according to the regulations, and the treatment of patients who have an influence on the test results during the study, the incomplete data affect the clinical efficacy observation.(5)Spontaneous bleeding tendency.

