### Randomization and blinding

2.4

The staff member will refer to a specific random number handbook generated by an independent statistician based on statistical software before study activation to determine the study intervention assigned to the randomized patient. The randomization schedule is layered by the position of each 4-bit variable block. Participants will be randomly assigned to 1 of the 2 groups in a 1:1 ratio after completion of baseline assessment, according to a randomized block list generated by an independent research assistant using R, and the code will be kept in opaque sequentially numbered envelopes. The treatment allocation codes will be enclosed by an independent research assistant in sequentially numbered opaque envelopes and will not be revealed until the participants have completed all baseline assessments and immediately before the first massage treatment. The single-blind method is adopted in this study, and there are two-level blind methods. First, blind evaluation, in which the participants are evaluated by a third party who does not know the grouping. Second, the blind statistical analysis, where the statistical data will be analyzed by statisticians with unclear grouping and its meaning. (Fig. 1)

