### Treatment protocol

2.5

1. Experimental group

1) Pediatric massage method:^[18]^

Place the child in a quiet, warm treatment room at room temperature between 25°C and 28°C. Appease the child before the operation to keep him in a quiet state.

Steps:②

Stimulation Governor Vessel and The Bladder Meridian of Foot-Taiyang. The child will take the prone position, the doctor will stand on the right side, and will use the Mofa along Governor Vessel direction to rub the entire spine, from top to bottom 3 to 5 times; Anrou the back of the first sideline and the second sideline of The Bladder Meridian of Foot-Taiyang by up to down 3 to 5 times; pinch the spine from top to bottom 3- 5 times; rubbing Shenshu (BL23), Mingmen (DU4), and Baliao.②

According to the principle of spinal neuroanatomy, the projection point on the surface of the spinal nerve root of children with spastic cerebral palsy will be determined, which will usually be the place with a cord or nodal reactants or the position of muscle tension and spasm, and the stimulation will be performed by rubbing for 3 min.③

Local treatment: According to the degree of spasm of the paralyzed limb, local treatment will be carried out using the traditional methods. The child will be placed in a supine position, and the doctor will use rolling to relax limbs, simultaneously, by the passive movement of the corresponding joint. Pressing will be performed to knead paralytic limb in turn, from top to bottom, applying gentle holding method to paralytic limb for 3–5 times. Following this, moderate shaking, pulling, or pulling to the corresponding joints of the paralyzed limb will be applied.④

Regulating yin and yang. The child will be placed in the supine position; the doctor will stand on the head side, opening the Tianmen 30 times, separate-pushing the Kangong 30 times, separate-pushing Ying Xiang (LI20) 30 times, kneading Taiyang (EX-HN5) for 1 min, and grasping Jianjing (GB21) 3 to 5 times. (Fig. 2)

(1)Basic rehabilitation treatment group(2)Treatment Procedure: 1 treatment per day, 5 times a week, 15 to 20 minutes each time, 4 weeks for a course of treatment, a total of 3 courses of treatment. To ensure the scientific and accurate results of the assessment, the assessment will be performed in a single-blinded manner, and all evaluations will be performed by a trained tutor.

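### The secondary overall-health total combines inquiry items, which caregivers who know the arm must answer, with examiner-observed signs, so the blind evaluation described for the trial covers only part of it.

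*Protocol article*

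**What the plan says.** Section 2.8 of the protocol article lists overall health as one of two secondary outcomes. The scale "will be used to record the symptoms of the children, such as diet, sleep, and diarrhea". Its content is drawn "from 4 aspects: inspection, auscultation and olfaction, inquiry, and pulse-taking and palpation of children", covering "the breath, color, shape, state, god, crying, eating, sleeping, mainland, and so on". The scoring rule is a single sum: "a comprehensive evaluation of various combined score values (single 2 points, a total of 27 items, maximum 54 points) will be performed".

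Section 2.3 sets the age: "Aged 1 to 3 years, both male and female children".

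On masking, section 2.4 describes "blind evaluation, in which the participants are evaluated by a third party who does not know the grouping", together with statisticians who do not know the grouping. Section 2.5 makes the scope general: "the assessment will be performed in a single-blinded manner, and all evaluations will be performed by a trained tutor". Neither section makes an exception for any outcome or item.

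The abstract and section 2.5 give the control arm basic rehabilitation alone, with no sham massage. Section 2.4 has the allocation opened after baseline assessment, just before the first massage.

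**The concern.** A masked assessor gives a masked outcome only when the assessor is also the source of the information. For signs that are seen, heard or felt, that is so. For inquiry items the assessor writes down what someone else says, and the rating carries whatever that person knows or expects.

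Here that person is a caregiver who knows whether the child is receiving massage. Families who bring a child to massage five days a week for 12 weeks may hope for better eating and sleep, and may report accordingly. Once these answers are added to the examiner's signs, a difference in the total does not show which source produced it. Followed as written, the plan would let a partly open-label total be reported as a blindly evaluated result.

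**Working it through.** **1. The plan's own figure.** 27 items × 2 points = 54. The stated maximum reproduces.

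**2. Who can supply the inquiry answers.**
- Inquiry is one of the four named aspects, and diet, sleep and diarrhea are named symptoms (section 2.8).
- The children are 1 to 3 years old (section 2.3). They cannot give a history of diet, sleep or bowel habit, and an examiner at one visit cannot observe these over the preceding weeks.
- The answers must therefore come from a caregiver. This is an inference from aspect and age; the article does not name the informant.

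**3. Whether the caregiver knows the arm.**
- The experimental arm has 5 massages a week in three 4-week courses: 5 × 12 = 60 sessions (section 2.5). The control arm has none and no sham.
- Only evaluators and statisticians are listed as masked (section 2.4).
- Caregivers will know the arm at weeks 4, 8 and 12. The baseline score is taken before allocation is opened and is not exposed in this way.

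**4. Against the blinding statement.** Sections 2.4 and 2.5 mask the assessor for all evaluations. Steps 2 and 3 show that this does not mask the source of the inquiry items. The total contains both kinds of item, so it is only partly blinded.

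**5. Whether the size can be worked out.** It cannot. The number of inquiry items, the reporting shift per item and the standard deviation (SD) of the total are all absent. The illustration below uses assumed values only, to show how wide the possibilities are.

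Take *k* informant items, a mean shift *b* per item favouring massage, no true effect and 82 per arm (section 2.2.1, before the allowance for loss). Then

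- shift in total = *k* × *b*
- standard error = SD × √(2/82) = 0.156 × SD
- chance of a significant result favouring massage = Φ(shift / standard error − 1.96), nominally 2.5%

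With *b* = 0.25 (assumed):

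| *k* (assumed) | Share of 54 points | Shift | SD 8 | SD 6 | SD 4 |
|---|---|---|---|---|---|
| 3 | 6 (11%) | 0.75 | 9% | 12% | 22% |
| 4 | 8 (15%) | 1.00 | 12% | 19% | 36% |
| 7 | 14 (26%) | 1.75 | 29% | 46% | 80% |

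Example: *k* = 4, SD 6 gives 1.00 / (0.156 × 6) = 1.07, and Φ(1.07 − 1.96) = 19%.

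With *b* = 0.1 the smallest value is 4% (*k* = 3, SD 8). With *b* = 0.5 the largest is close to 100% (*k* = 7, SD 4). The spread reflects the assumptions and is not an estimate for this trial.

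**The case against.** The strongest reply is that the trial calls itself single-blind, never says that parents are masked, and states only that the third-party evaluator does not know the grouping. As a statement about the assessor that can be true. This stands: section 2.4 is not false, and the point is about how far it reaches. It does not remove the concern, because section 2.5 applies single-blinded assessment to all evaluations and nothing tells a reader that one outcome rests partly on unmasked informants.

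A second reply is that the item list, the instructions on whom to ask and any domain scores belong in the full protocol, the case report form or the analysis plan. This also stands, so their absence is not held against the article. What the article does fix is the single combined score and the unqualified description of blinding.

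Three stronger readings are tempting, and the documents do not support them:
- *That the two sources can never be separated.* The article says that a combined score will be evaluated. It does not say that item scores are discarded, and subscores can be formed if they are kept.
- *That crying and stool are also caregiver-reported.* No item is assigned to an aspect. Crying can be heard by the examiner, and stool is not listed as such: the text has diarrhea and one garbled word in the list. Diet, sleep and diarrhea are enough for the point.
- *That a benefit could come wholly from caregivers' expectations, with a stated false-positive rate.* Any such rate only returns the item count, shift and SD that were put in.

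Finally, dropping the inquiry items or demoting the scale would change a construct meant to span all four aspects. That objection is fair, and the fix below does neither.

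**Conclusion.** The point holds in a limited form. The overall-health total mixes examiner-observed signs with inquiry items that caregivers aware of the arm must in practice answer, so the assessor is masked but the total is only partly blinded. The conclusion rests on two inferences, both well supported by the article: children aged 1 to 3 cannot answer inquiry items themselves, and caregivers know the arm when there is no sham.

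The likely direction is in favour of massage, on the assumption that caregivers expect benefit. The size is unknown and cannot be derived from the article. Only this secondary outcome is concerned; the primary outcomes (modified Ashworth scale and gross motor function) and the sample size are not affected by this point. The change is worth making because it is cheap and prevents an over-claim, but it does not threaten the trial's main conclusion.

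**What to change.** In sections 2.8 and 2.12:

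1. Keep the 54-point total as the secondary outcome.
2. Prespecify which of the 27 items belong to each of two subscores, and report both beside the total: examiner-observed (inspection, auscultation and olfaction, pulse-taking and palpation) and inquiry.
3. State that caregivers answer the inquiry items, and that the inquiry subscore and the total therefore rest wholly or partly on unblinded report.
4. Limit the blind-evaluation statement for this outcome to the examiner-observed subscore, with a matching qualification in sections 2.4 and 2.5.
5. Do not claim a blinded benefit on overall health unless the examiner-observed subscore supports it.

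No new visits or measurements are needed, provided that the item scores are kept as well as the sum. The cost is two extra scores to report and a slightly weaker blinding claim.

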### Safety assessments

2.9

All the adverse events (AEs) will be monitored and recorded by researchers throughout the treatment. AEs will be coded using the World Health Organization Adverse Reaction Terminology Dictionary. Skin lesions and rashes are common side effects of massage. Once the AEs occur during the treatment, the time and severity of the treatment will be recorded in detail, and the cause will be analyzed, and the correlation between the AE and trial will be evaluated. If any serious AE occurs, it will be reported to the Human Research Ethics Committee of YNTCM. It will judge whether this child can continue this study. Special attention will be given to those participants who have discontinued treatment owing to AEs or those experiencing serious AEs.

### Reasons for withdrawal

2.10

When a participant withdraws before completing the study, the reasons for withdrawal will be recorded.

### Monitoring

2.11

#### Data and safety monitoring plan

2.11.1

A Data and Safety Monitoring Board will be set up to monitor research progress and review the safety and quality of data. Details of all information will be recorded using the Case Report Form. The committee will consist of 3 members, including a senior massage practitioner, cerebral palsy specialist, and biostatistician. The Data and Safety Monitoring Board is independent of the proposed study, and all the committee members will have to declare any conflict of interest in the study. Regular board meetings will be held to ensure that the data are collected scientifically and ethically, and participants are not exposed to unnecessary risks.

The audit of test conduct will be conducted monthly, and the process will be independent of the investigators and sponsors.

### Statistical analyses^[25]^

2.12

The primary analysis will be performed using intention-to-treat methods and therefore include all randomized child data. All data will be checked into the double machine using Epidata 3.1 software for database management.

Specific statistical analysis methods: The baseline characteristics of patients in the 2 groups will be reported using frequency distribution and descriptive statistics (including measurements of concentration trends and dispersion). The main analysis of the comprehensive measurement of the rate of counting data will be the chi-square test. Two independent samples of the *t*-test will be performed between the 2 groups. The paired t-test will be used to compare the outcome variables of each treatment group before and after the treatment. The difference between the multiple measurements of the same group will be conducted using the multiple measures data analysis of variance, combined with logistic regression analysis to examine the adjustment effect of clinically relevant covariates, which will be the results (gender, birth weight, gestational age). We will also follow the pre-specified subgroup analysis. All analyses will be performed using the R software. The aforementioned steps will be monitored by the third-party tests, and the quality control of the test will be carried out. The blind law is unified and responsible.

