#### Sample size estimation

2.2.1

The estimated sample size will be compared using 2 sets of odds ratios. The formula is as follows:$$n_{1}={\left[\frac{z_{1}-\alpha /2\sqrt{\bar{p}\bar{q}(1+1/r)}+z_{1}-\beta \sqrt{p_{1}q_{1}+p_{2}q_{2}/r}}{\Delta }\right]}^{2}=82$$

A total of 182 children were calculated using the transcript estimation method for the robustness of the clinical trial. The specific index is that α = 0.05 on both sides of the tail, and (1-β) is 0.80, and the absolute difference of the comprehensive result variable index is 20%. Our initial estimate of the sample size is 82, and the loss rate is increased by 10%, and 91 is determined for each group. Thus, the 2 groups totaled 182.^[13,14]^

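### The primary analysis is said to include all randomized children, but exclusion criterion 4 removes non-completers and incomplete data, and the named between-group tests do not bring them back

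*Protocol article*

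**What the plan says.** **Analysis population.** Section 2.12 (Statistical analyses) opens with "The primary analysis will be performed using intention-to-treat methods and therefore include all randomized child data".

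**Exclusions.** Section 2.3 (Subject recruitment), exclusion criterion 4, combines several grounds. Besides not meeting the inclusion criteria, it names failing to complete the study as required, receiving treatment during the study that affects the results, and cases where "the incomplete data affect the clinical efficacy observation".

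**Tests.** Section 2.12 names these:
- For a rate: "The main analysis of the comprehensive measurement of the rate of counting data will be the chi-square test".
- For the treatment comparison, two-sample t-tests that "will be performed between the 2 groups".
- Within each arm: "The paired t-test will be used to compare the outcome variables of each treatment group before and after the treatment".
- Also within each arm: "The difference between the multiple measurements of the same group will be conducted using the multiple measures data analysis of variance".
- Logistic regression to adjust for covariates.

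**Expected loss.** Section 2.2.1 (Sample size estimation) starts from 82 per group and says "the loss rate is increased by 10" per cent, which gives 91 per group and 182 in total.

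**Visits and withdrawal.** Section 2.6.1 schedules all outcomes at baseline and weeks 4, 8 and 12. Section 2.10 says that reasons for withdrawal are recorded and does not mention assessment after withdrawal. Section 2.4 blinds the evaluators and the statisticians only.

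**The concern.** Two statements about the same children disagree. Section 2.12 keeps every randomized child in the primary analysis. Criterion 4 takes out children who did not finish or whose data are incomplete. An analyst who applies criterion 4 and then runs the named tests would analyse completers and, following section 2.12, call the result intention-to-treat.

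The label matters because loss in this trial need not be unrelated to treatment. Massage is given by hand, five days a week for 12 weeks, so families and therapists know the arm. A family that sees little early benefit may stop. If that happens more in one arm, the children left in that arm are a selected group, and randomization no longer protects the comparison.

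**Working it through.** **1. The plan's own sample size.** Inputs from section 2.2.1: two-sided alpha 0.05, power 0.80, absolute difference 20 points, ratio 1:1. The two rates are not given; 60% and 80% are assumed here (20% and 40% give the same result). With a mean rate of 0.70, the printed formula gives

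n = [(1.96 × √(0.70 × 0.30 × 2) + 0.842 × √(0.60 × 0.40 + 0.80 × 0.20)) / 0.20]² = [(1.270 + 0.532) / 0.20]² ≈ 81.2, so 82 per group.

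For loss, 82 / 0.90 = 91.1 and 82 × 1.10 = 90.2. The stated 91 agrees within rounding.

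**2. The two sections side by side.** Section 2.12 includes all randomized children. Criterion 4 excludes for non-completion and for incomplete efficacy data. Both grounds arise only once a child is in the study, and the neighbouring ground refers expressly to treatment during the study. So criterion 4 acts on children already randomized.

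**3. What each named method needs.**

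| Method | Role in section 2.12 | Child is lost if |
|---|---|---|
| Chi-square | Main analysis of a rate | the outcome is not classified |
| Two-sample t-test | Between groups | the value tested is missing |
| Paired t-test | Within each arm | the before or after value is missing |
| Repeated-measures ANOVA (classical) | Within each arm | any one visit is missing |

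**4. Children leaving the between-group comparison.** Take week 12 as the visit tested (section 2.12 does not name it). 182 × 0.10 = 18.2 children leave, and 91 × 0.90 = 81.9 per group remain.

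**5. Power.** With the same formula, at 60% versus 80%: 0.84 with 91 per group and 0.80 with 81.9. At 40% versus 60%: 0.77 and 0.73. The drop due to the planned loss is about 0.04 in each case.

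**6. Possible bias.** Assumptions, none from the document: correlation 0.7 between visits, loss at random in the control arm, 6–10% loss in the massage arm, and logistic drop-out in the massage arm, more likely with a worse week-4 score. A simulation of 3,000 trials with 91 per arm and slopes 0.5, 1.0 and 1.5 gives a completers' week-12 bias of 0.025, 0.049 and 0.085 SD. Repeating it across the loss range gives 0.02 to 0.085 SD. Here the bias favours massage; it would reverse if the better responders left.

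For scale, the standard error of a mean difference with 82 per arm is √(2/82) = 0.156 SD. The difference detectable with 80% power is 2.80 × 0.156 = 0.44 SD. The bias is therefore about 5% to 19% of that difference.

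**The case against.** The article condenses a fuller protocol, and the method for missing values may sit there or in a statistical analysis plan. A t-test or chi-square test after imputation includes everyone, and a child without an outcome can be counted in a rate, for example as a non-responder. Intention-to-treat also means analysis as randomized, which none of these tests prevents. All of this stands. The test names alone do not prove that the property is lost, and silence on imputation is no fault here. What it does not answer is criterion 4: an imputation rule elsewhere would still conflict with a stated exclusion of children with incomplete data.

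Three stronger readings might be inferred, and the document does not support them.

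- **That every named test drops every child with a missed visit.** This describes classical repeated-measures ANOVA only. The t-tests lose only children who lack the value tested.
- **That ANOVA deletion damages the treatment comparison.** With 10% loss and a further 3–5% missed at each of three visits (assumed), 182 × [1 − 0.90 × (1 − m)³] gives 32 to 42 children, or 18–23%. But section 2.12 assigns this ANOVA to measurements within the same group, so those counts do not bear on the between-group result.
- **That the trial loses its power.** The inflation to 91 per group already allows for the 10%.

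It is also fair to say that the bias is modest and rests on assumed inputs.

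**Conclusion.** The point holds as a contradiction within the document. Section 2.12 promises an analysis of all randomized children; criterion 4 in section 2.3 removes some of them for reasons that arise after randomization; and the chi-square and two-sample t-tests, as named, do not restore them. Followed as written, about 18 of 182 children would leave the final-visit comparison at the planned loss, and a completers' result would carry an intention-to-treat label.

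The count of 18 rests on the plan's 10% and on week 12 being the visit tested. The harm is possible bias rather than lost power. The range of 0.02 to 0.085 SD illustrates one drop-out pattern and is not an estimate for this trial. The change should be made, but the point does not show that the treatment comparison is invalid.

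**What to change.** 1. **Reconcile sections 2.3 and 2.12.** Remove failure to complete and incomplete data from exclusion criterion 4, so that neither takes a randomized child out of the primary analysis.
2. **Continuous outcomes.** For the GMFM score, and for the Ashworth score if analysed as 1–6 points, replace the unadjusted two-sample t-test with the week-12 contrast from a mixed model for repeated measures. Fit it to all available week 4, 8 and 12 values, with arm, visit, arm-by-visit, baseline value and centre. With baseline as a covariate, a child with no post-baseline value adds nothing; if such children must contribute, model baseline as one of the responses.
3. **The rate.** For the chi-square comparison, keep all randomized children in the denominator by imputing missing outcomes under a stated rule.
4. **Follow-up and sensitivity.** Continue the scheduled assessments in children who stop treatment. Add one sensitivity analysis that shifts unobserved massage-arm values unfavourably.

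The cost is wording, a standard model in R (the software already named) and some extra effort to keep children in assessment. No new visits or measurements are needed.

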**Methods/Design::**

The study will be a multicenter, single-blinded, randomized-controlled pilot trial. During the period from June 2019 to December 2020, 182 children with spastic cerebral palsy will be randomly divided into experimental and control groups in a 1:1 ratio. The experimental group will undergo the modified selective spinal massage method combined with the basic rehabilitation treatment, while only the basic rehabilitation treatment would be performed for the control group. The intervention period of the study will last 12 weeks, 5 days weekly on weekdays. The primary outcomes include a modified Ashworth scale assessment and gross motor function test. The secondary outcomes include the 4-diagnostic scale of Chinese medicine and children's intelligence. The observation index will be measured during the complete 12 weeks duration after the treatment of the child, that is, before treatment, after 4 weeks of treatment, after 8 weeks, and after 12 weeks of treatment.

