### Primary outcome measure

2.7

1.Modified Ashworth ScaleOwing to the presence of sputum, quadriplegia, and hemiplegia, the lower limb muscle tone (triceps, soleus, gastrocnemius) will be assessed using a modified Ashworth scale.^[19,20]^ It includes 6 rating levels, 0, 1, 1+, 2, 3, and 4. For statistical convenience, 0, 1, 1+, 2, 3, and 4 levels of the muscle tension level in the scale will be determined to be 1, 2, 3, 4, 5, and 6 points, respectively. All subjects are guaranteed not to be treated with any muscle relaxants. During the evaluation, efforts should be made to avoid position metastasis, skin irritation, low ambient temperature, emotional agitation, pain, urinary tract infection, or urination before the examination. If there is a clonic or transient paroxysmal contraction, test again after the disappearance.2.Gross motor function rating scale (GMFM)

The gross motor function score will be evaluated using the GMFM for gross motor function evaluation. GMFM currently has 88 versions (GMFM-88) and 66 items (GMFM-66).^[21]^ GMFM-88 is a sequential scale, each using a 4-level scoring method, divided into 5 functional areas: Area A (lying position and turning over), a total of 51 points (17 items); Area B (sitting), total score 60 points (20 items); Area C (crawling and squatting), total score of 42 points (14 items); Area D (station), total score 39 points (13 items); Area E (walking, running and jumping). The total score is 72 points (24 items). The evaluation results include 5 functional distinction values and total scores expressing the corresponding energy regions and overall gross exercise capacity, respectively. The Chinese translation is based on the 1993 GMFM revision. Evaluate 3 designated physicians or therapists to perform in a quiet, independent, well-lit room. The room temperature will be controlled at 20°C to 30°C, and the children's clothes will be 1 to 2 layered. In the absence of a violation of the assessment requirements, the same family members should be present in each assessment to encourage the child to perform at an optimal level.

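### The main analysis and the sample size are set for an overall rate that is not a declared outcome, and no between-group analysis of the two primary scores is named as decisive

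*Protocol article*

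**What the plan says.** **Outcomes.** The abstract states: "The primary outcomes include a modified Ashworth scale assessment and gross motor function test". Section 2.7 describes MAS thus: "It includes 6 rating levels, 0, 1, 1+, 2, 3, and 4", and recodes these levels to 1 to 6 points. For GMFM it says: "The evaluation results include 5 functional distinction values and total scores". The five GMFM-88 area maxima add up to 51 + 60 + 42 + 39 + 72 = 264 points. The secondary outcomes in section 2.8 are a Bayley developmental scale and a four-diagnostic scale with a maximum of 54 points. Neither section defines a responder, an effective rate or a cut-off.

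**Analysis.** Section 2.12 says: "The main analysis of the comprehensive measurement of the rate of counting data will be the chi-square test". The next sentences read: "Two independent samples of the *t*-test will be performed between the 2 groups" and "The paired t-test will be used to compare the outcome variables of each treatment group before and after the treatment". A repeated-measures analysis of variance follows, described for measurements within the same group, "combined with logistic regression analysis to examine the adjustment effect of clinically relevant covariates" (gender, birth weight and gestational age).

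**Sample size.** Section 2.2.1 uses the formula for two proportions with two-sided alpha 0.05, power 0.80 and an absolute difference of 20% in an overall outcome index. This gives 82 per arm, and 91 per arm after 10% loss. The two proportions are not stated.

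**The concern.** Two sections assume a rate: section 2.12 for the main test and section 2.2.1 for the sample size. The outcome sections contain only scores. If the chi-square test is the main analysis, it answers a question about an endpoint the article does not declare, and the declared primaries have no designated test. Whoever analyses the trial could then take as the result either a t-test at any of three post-baseline visits or a rate built from the scores. That leaves room for selective reporting. Cutting a score into two classes also gives up power.

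**Working it through.** **1. Reproducing the stated size.** The section 2.2.1 formula at 1:1 allocation is

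n = [1.96·√(2·p̄·q̄) + 0.8416·√(p1q1 + p2q2)]² / Δ², with Δ = 0.20.

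The article gives no p1 or p2, so these are assumed. For 20% vs 40%, p̄ = 0.30:
- 1.96·√0.42 = 1.270
- 0.8416·√(0.16 + 0.24) = 0.532
- n = (1.802/0.20)² = 81.2, rounded up to 82

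By symmetry, 60% vs 80% also gives 82. With control rates from 5% to 75% and the same difference, n runs from 49 to 97 per arm. For loss, 82 × 1.1 = 90.2 and 82/0.9 = 91.1, so the stated 91 is in line. The stated size is therefore that of a binary endpoint.

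**2. Matching each listed method to the declared primaries.**

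| Method in 2.12 | Compares the arms? | Tied to a primary outcome and visit? | Called main? |
|---|---|---|---|
| Chi-square on an overall rate | yes | no; the rate is undefined | yes |
| Two-sample t-test | yes | no | no |
| Paired t-test | no, within arm | outcome variables in general | no |
| Repeated-measures ANOVA | no, within group | no | no |
| Logistic regression | not stated | no | no |

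No row both compares the arms on MAS or GMFM and is designated as decisive. A chi-square test does not suit the GMFM total. It can be run on the six MAS levels as a 2×6 table, but it then ignores their order.

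**3. What the fixed size gives on a score.** The article gives no SD or mean difference, so the result is in SD units. The detectable difference is (z for alpha + z for power)·√(2/n):
- 82 per arm, two-sided 0.05: (1.960 + 0.842)·√(2/82) = 2.802 × 0.1562 = 0.44 SD
- 91 per arm: 0.42 SD
- 82 per arm with alpha split over two primaries (0.025 each): (2.241 + 0.842) × 0.1562 = 0.48 SD

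For assumed effects of 0.3, 0.4 and 0.5 SD, 80% power needs 175, 99 and 63 per arm.

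**4. Cost of dichotomising (illustration).** Assume a normal score split at its median, so the two class proportions are Φ(d/2) and Φ(−d/2). With 82 per arm:
- d = 0.44: proportions 0.587 and 0.413, difference 0.174. Power = Φ[(√82·0.174 − 1.96·√0.5)/√(2·0.587·0.413)] = Φ(0.27) = 61%. The t-test (non-central t) has 80%.
- d = 0.40: proportions 0.579 and 0.421, difference 0.159. Power = Φ(0.07) = 53%. The t-test has 72%.

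The loss is about 19 percentage points in each case.

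**The case against.** The strongest reply is that section 2.12 does contain methods for scores. The sentence after the chi-square statement gives a two-sample t-test between the groups. The chi-square sentence is also garbled. It may mean only that categorical data are mainly tested by chi-square, with the t-test serving measured data. The first part is right, so a reader should not infer that the plan has no test for its primaries. The second reading is possible, although the two-proportion formula in section 2.2.1 speaks against it. It would not remove the problem: no main analysis would then be named for either primary, and the trial would still be sized on an undefined rate.

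Three stronger inferences are tempting, and the article does not support them.
- **That the named methods cannot be applied to either primary.** Chi-square can be run on the six MAS levels, and logistic regression has an ordinal form. The mismatch is complete only for the GMFM total.
- **That a cut-off will be chosen after the data are seen.** This is a risk. A responder definition may stand in the full protocol or an analysis plan, neither of which is shown.
- **That the trial was planned on 60% vs 80%.** The article states only the 20% difference, and 20% vs 40% gives the same 82.

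Nor can the point be set aside as detail left to an analysis plan. The article names a main test and a sample-size endpoint, and neither corresponds to its declared primaries.

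**Conclusion.** The point holds as an inconsistency within the article. The main test and the sample size refer to an overall rate that is not among the outcomes, and no between-group analysis of MAS or GMFM is designated as decisive. That conclusion rests on the text alone.

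The power figures (80% vs 61%, 72% vs 53%) are illustrative. They assume a normally distributed score and a median split, which the article does not propose, and they do not describe a six-level MAS. The 0.44 SD figure needs only the stated alpha, power and 82 per arm, under the usual normal approximation for two means. Whether 0.44 SD is a realistic effect on either scale cannot be judged, because the article gives no SD.

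**What to change.** **Section 2.12.** Name as main analysis the between-group difference at week 12 in the GMFM-88 total score (linear model) and in MAS (ordinal model), each adjusted for its own baseline value. Enter gender, birth weight and gestational age in these same models in place of a separate binary logistic regression. Keep chi-square for truly binary items such as adverse-event incidence, or for a responder outcome whose definition and cut-off are fixed before unblinding. Defining the overall rate and declaring it primary would also reconcile the text, but it keeps the power loss of a dichotomy.

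**Section 2.2.1.** State what the fixed size delivers on a score: 82 evaluable children per arm detect about 0.44 SD with 80% power at two-sided 0.05, or about 0.48 SD if alpha is split over the two primaries. Say openly that the two proportions behind the 82, and an SD for either scale, were not given.

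**Cost.** Both sections are reworded, and the sample-size justification must be restated on the score scale. No new data or patients are needed.
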